### Ethical Considerations

This research is exempt from Research Ethics Board (REB) review because the data to be used are authorized under Section 45 of Ontario’s Personal Health Information Protection Act (PHIPA), which allows for the use of personal health information for health system evaluation and planning without requiring REB review [48]. The data will be analyzed at ICES [17], an independent, not-for-profit research institute authorized under PHIPA to collect and use personal health information without consent for these authorized purposes. Individual consent from Ontario residents will not be required for this study, as ICES’s legal status under PHIPA authorizes the secondary use of provincial health care records.

All analyses will be performed at ICES using linked, coded (deidentified) data. Researchers will not have access to any identifiable personal information, and strict privacy and security safeguards will be in place to protect confidentiality. No compensation will be provided, as this study will use existing health administrative data and will not involve direct participant recruitment or interaction. This study will not include images, videos, or any identifiable information from individual participants. On completion, the results of this population-based study will be submitted to a peer-reviewed biomedical journal for publication and presented at relevant conferences.

## Results

In a preliminary analysis, we identified approximately 3.8 million older adults who filled prescriptions for over 500 unique medications during the study period. Each drug can serve as drug A or drug B in various combinations, resulting in approximately 200,000 potential drug pairs for analysis. The initial drug pair cohorts had a median of 583 new users per cohort (IQR 237-2130), with a median overlap duration of 57 days (IQR 30-90). For example, in a chronic-chronic drug pair cohort where levothyroxine was drug A and rosuvastatin was drug B, the median overlap duration was 135 days among 128,762 patients, with 73.1% (n=94,036) females and a median age of 66 years. In a chronic-acute drug pair cohort (eg, levothyroxine as drug A and amoxicillin trihydrate as drug B), the median overlap was 10 days among 197,057 patients, with 74.8% (n=147,399) females and a median age of 67 years. In an acute-chronic drug pair cohort (eg, amoxicillin trihydrate as drug A and rosuvastatin as drug B), the median overlap was 10 days among 2702 patients, with 51.6% (n=1394) females and a median age of 66 years. Lastly, in an acute-acute drug pair cohort (eg, amoxicillin trihydrate as drug A and ciprofloxacin as drug B), the median overlap was 10 days among 4220 patients, with 59.4% (n=2507) females and a median age of 70 years. The protocol, finalized on August 30, 2025, outlines the analysis of data from 2002 to 2023. The high-throughput computing analysis is planned for completion by fall 2026, and findings from the analysis will be assessed in 2027 for clinical relevance by integrating PK, PD, and epidemiological evidence, supported by clinical validation tools. The final results will be prepared for dissemination, with manuscript submission planned for December 2028.

## Discussion

### Summary

This study aims to identify harmful DDIs by analyzing Ontario health care databases using high-throughput computing. We will process data from over 3.8 million residents aged 66 years and older, evaluating more than 200,000 medication pairs and examining associations with 74 acute outcomes, including hospitalizations, emergency department visits, and mortality. High-throughput computing will enable us to identify and test thousands of medication combinations. We will compare individuals prescribed medication pairs with those on single medications, using propensity score methods to balance comparison groups on over 400 baseline health characteristics. We will conduct extensive sensitivity and bias analyses to ensure that potential signals are not artifacts of statistical or methodological bias. Additionally, machine learning algorithms will be used to complement the high-throughput computing approach.

High-throughput computing and automated analytical pipelines have proven effective for detecting potential DDIs in large health care datasets in other countries, such as the United States. Previous studies by Bykov et al [14] and Leonard et al [15] have demonstrated that these methods can efficiently confirm known interactions and identify novel signals. However, these approaches have largely been limited to single-object drugs, specific outcomes, or nonrepresentative datasets (derived from a specific subset of the population, such as those with a certain type of insurance, rather than the entire population), which may restrict generalizability. Building on these advances, our study will use high-throughput computing to analyze Ontario’s population-based, linked administrative databases, which capture comprehensive prescription and outcome data across the province’s universal health care system. Using a population-based, new-user cohort design, we will systematically evaluate nearly 200,000 medication pairs among 3.8 million older adults—an effort that would be impractical with traditional methods. This approach will not only fill a critical gap by providing large-scale, real-world evidence in a Canadian context but also enhance generalizability, generate signals that could inform clinical decision-making once validated, and strengthen postmarketing pharmacovigilance efforts for older adults. To the best of our knowledge, this represents the first application of such an approach in Canada, leveraging the strengths of a universal health care setting to further enhance the generalizability and clinical relevance of detected DDI signals.

The cohort study is designed to mimic typical clinical scenarios, for example, an individual who has been taking digoxin for 7 months and is then newly prescribed sulfamethoxazole-trimethoprim to treat a urinary tract infection. In DDI studies, such scenarios are categorized as follows:

Precipitant triggered: Individuals initiate the object drug first, followed by the precipitant, with follow-up starting on the day the precipitant is initiated.Object triggered: Individuals initiate the precipitant first, followed by the object drug, with follow-up starting on the day the object is initiated.

Our approach will be hypothesis free since it does not assume beforehand whether drug A or drug B will function as the object or the precipitant. Analyzing initiation orders separately is highly recommended in traditional DDI studies—if feasible—as it addresses different clinical questions, better controls confounding, and increases the validity of the results [2].

### Strengths of the Study

A key strength of this study is the use of Ontario’s administrative health care databases. These databases include comprehensive, encrypted data on health care visits, hospitalizations, lab results, and prescription records for residents aged 65 years and older [17]. This extensive data coverage enables the capture of a wide range of adverse outcomes, providing a detailed picture of the potential risks associated with specific drug interactions [16].

The application of high-throughput computing and automation will significantly enhance the efficiency and scalability of our analyses [49]. This approach will allow us to simultaneously evaluate numerous drug interactions, which would be impractical using traditional methods. By automating the creation of cohorts and statistical analysis, we can quickly and accurately identify potential DDIs, facilitating more rapid updates to clinical guidelines and regulatory policies [4,50].

### Challenges and Limitations

Despite using advanced statistical techniques to control for confounding, residual confounding may still be present [51]. Factors that are not captured in the administrative data or that are measured with error could bias our results [52]. To address this, we will conduct multiple sensitivity analyses and use negative control outcomes to assess the robustness of our findings [37].

Our study focuses on acute (30-day) outcomes, which will not capture the effect of long-term exposure [53]; however, we will conduct additional analyses to assess longer follow-up times.

The study is designed to identify harmful DDIs with a moderate-to-high risk in magnitude in cohorts of at least 1000 individuals, and therefore, it will have limited statistical power to detect small risk increases.

Our study does not include data on nonprescription (over-the-counter) drugs, drugs prescribed in hospitals, or comprehensive outpatient prescription drug use in children or adults aged under 65 years. These exclusions may limit the generalizability of our findings to a broader population. However, the focus on older adults is justified, given their higher risk of polypharmacy and adverse drug interactions.

Given the large number of comparisons being made, there is a risk of spurious findings due to multiple testing [16]. To mitigate this, we will apply the Benjamini-Hochberg procedure to control the false discovery rate and use E-values to assess the robustness of our findings against unmeasured confounding [31].

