#### Cohort-Level Exclusion Criteria

To ensure meaningful results, only cohorts with a minimum sample size of 1000 patients, with at least 200 individuals in the exposed group and 200 individuals in the referent group, will be considered for further analysis.

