### Outcomes

We will examine 74 outcomes within 30 days of cohort entry (Textbox 1). The outcomes were chosen using a prespecified analytic approach and considering the clinical significance of the outcomes and the observed rates in the study region [16]. Many of the algorithms used to identify these outcomes have been validated in previous studies and demonstrate high sensitivity and specificity [26-30]. Shorter and longer follow-up times for outcomes will be examined in additional analysis (see the *Additional Analysis to Characterize the Signals* section).

Final set of 74 clinically relevant outcomes (ordered alphabetically).

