#### Regression Analyses

A visual summary of the regression and additional exploratory analyses is provided in Multimedia Appendix 4. In each cohort, outcomes will be eligible for analysis if there are at least six outcome events in both the exposed and referent groups. Reporting fewer than six events could lead to potential patient reidentification and substantial estimation errors.

For each eligible cohort, we will use a modified Poisson regression model [36] to estimate the weighted risk ratio (RR) and its 95% CI for each outcome in the exposed group compared to the referent group. Additionally, a binomial regression model with an identity link function will be used to estimate the weighted risk difference (RD) and its 95% CI. If all 74 outcomes for a particular cohort are eligible, up to 74 regression models will be run.

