#### Criteria for Identifying Potential Signals of Harmful DDIs

Associations between a drug pair and an adverse outcome that meet the following criteria will be considered potential signals of harm and analyzed further:

Thresholds for RRs and RDs. The lower bound of the 95% CI for the RR must be ≥1.33, and for the RD, it must be ≥0.1%. These thresholds were chosen to ensure that only clinically significant increases in risk (of sufficient magnitude to be of concern) are considered. This analysis will focus solely on potential harms from drug combinations rather than protective benefits.Statistical significance. The *P* values from the modified Poisson regression model (for RRs) and the binomial regression model (for RDs) must be statistically significant after applying the Benjamini-Hochberg correction. This correction accounts for multiple comparisons across all outcomes and drug pair cohorts. The false discovery rate will be set at 5%, and the highest *P* value below the Benjamini-Hochberg critical value will be considered statistically significant, along with all *P* values below it. This correction will minimize the risk of false-positive discoveries (type I errors).

Drug pair cohorts that do not generate significant signals will not undergo further analysis.

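### The stated ability to identify moderate-to-high risk increases in cohorts of at least 1000 is not delivered at that floor: under the protocol's own signal rule a doubling of risk is usually missed there unless the outcome is very common

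*Protocol article*

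**What the plan says.** The capability is stated in the protocol article, Challenges and Limitations: "The study is designed to identify harmful DDIs with a moderate-to-high risk in magnitude in cohorts of at least 1000 individuals". The same sentence infers from this that power is limited for small risk increases. It names no other shortfall, and it does not put a number on moderate-to-high.

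The rule that produces a signal is set out in three places in the Methods:

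- Cohort-Level Exclusion Criteria: "a minimum sample size of 1000 patients, with at least 200 individuals in the exposed group and 200 individuals in the referent group".
- Regression Analyses: "outcomes will be eligible for analysis if there are at least six outcome events in both the exposed and referent groups".
- Criteria for Identifying Potential Signals of Harmful DDIs: "The lower bound of the 95% CI for the RR must be ≥1.33, and for the RD, it must be ≥0.1" (percent for the RD). Significance after Benjamini-Hochberg correction across all outcomes and cohorts is also required: "The false discovery rate will be set at 5" (percent).

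The criteria section adds that cohorts without a significant signal are not analyzed further. On typical size, the Results section reports: "The initial drug pair cohorts had a median of 583 new users per cohort (IQR 237-2130"). The article gives no 30-day outcome rates and no power figure.

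**The concern.** The limitation sentence ties a detection capability to a cohort size, but the signal rule asks for much more than a significant difference. The lower confidence limit, not the estimate, must clear 1.33, and six events are needed in each group. With 200 exposed patients, six events already mean an observed 30-day risk of 3% (6/200). With 583 they mean about 1% (6/583).

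At stake is what a non-signal means. Cohorts without a signal go no further, and all outputs are to be opened to users through a visualization tool. A reader who relies on the limitation sentence could take a missing signal in any cohort of 1000 or more as evidence against a moderate or large harm. Near the floor the data often could not have produced a signal for a true doubling of risk.

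**Working it through.** There is no power figure in the article to reproduce, so the check is a direct calculation from the written rule.

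**Inputs from the article.** Floor of 1000 in total with at least 200 per group; at least six events per group; 95% lower limits of 1.33 (RR) and 0.1% (RD); 30-day outcomes; median 583 new users (IQR 237-2130) in the initial cohorts.

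**Assumptions.** True RR of 2, with 3 and 4 as a range; referent 30-day risk p0 from 1% to 20%; 200/800 as the main split of the floor, with other splits checked; for the median cohort, 10 referents per exposed patient. The article fixes none of these.

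**Method.** Two independent binomials, enumerated exactly. With a and b events among n1 exposed and n0 referent patients, a signal requires all of the following:

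- a ≥ 6 and b ≥ 6
- ln[(a/n1)/(b/n0)] − 1.96·√(1/a − 1/n1 + 1/b − 1/n0) ≥ ln 1.33
- (q1 − q0) − 1.96·√(q1(1−q1)/n1 + q0(1−q0)/n0) ≥ 0.001, with q1 = a/n1 and q0 = b/n0

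Benjamini-Hochberg is left out because its realised cut-off cannot be known in advance; adding it can only lower the figures. Precision lost through trimming and weighting is also ignored, which favours the protocol.

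**Probability of a signal, 200 exposed / 800 referent**

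| True RR | p0 = 1% | 2% | 5% | 10% | 20% |
|---|---|---|---|---|---|
| 2 | 3.4% | 16.4% | 34.8% | 62% | 94% |
| 3 | 17% | 57% | 93% | >99% | >99% |
| 4 | 39% | 87% | >99% | >99% | >99% |

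**Cross-check by normal approximation,** RR = 2 and p0 = 5%: SE = √(0.90/(200×0.10) + 0.95/(800×0.05)) = √(0.045 + 0.02375) = 0.262. Then (ln 2 − ln 1.33)/0.262 − 1.96 = 0.408/0.262 − 1.96 ≈ −0.40, and Φ(−0.40) ≈ 34%. This agrees with 34.8%.

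**Other splits of 1000,** RR = 2, at p0 = 1% and 5%: 300/700 gives 2.3% and 40.1%; 400/600 gives 0.7% and 41.9%; 500/500 gives 0.05% and 40.1%; 800/200 gives 0.0% and 13.0%. None reaches 50%. With 200 exposed and 10,000 referents the figures are 5.2% and 46.3%, so more referents do not remove the problem.

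**How much the rule itself costs.** A plain two-sided 5% test at 200/800 and RR = 2 would have 26% power at p0 = 1% and 72% at 5%.

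**Median-size cohort,** 583/5830, RR = 2: about 8% at p0 = 0.5%, 26% at 1% and 45% at 2%. For RR = 3: 37% at 0.5% and 79% at 1%.

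**RR with 80% power against the 1.33 limit alone,** solving ln(RR/1.33) = 2.80·SE: at 200/800, 4.9 (p0 = 1%), 3.6 (2%) and 2.6 (5%); at 583/5830, 3.6 (0.5%) and 2.9 (1%).

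**Where the RD floor takes over.** Even in an unlimited sample, p0(RR − 1) must be at least 0.001, so RR must be at least 1 + 0.001/p0. This equals 1.33 at p0 = 0.001/0.33 ≈ 0.3%. Below that risk the RD floor is the binding one: RR 2 at p0 = 0.1%, RR 11 at 0.01%.

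**The case against.** The strongest reply is that this is one sentence in a limitations section. It describes a design target, and it leaves moderate-to-high undefined. RR = 2 and the risks are the reviewer's choice, and at the same floor the rule works well for RR = 3 at 5% risk (93%), RR = 4 at 2% (87%) and RR = 2 at 20% (94%). Several of the 74 outcomes, such as any physician visit or any emergency visit, may well be common. This limits the point to the conditions stated. It does not save the sentence: RR = 2 lies well above the 1.33 that the protocol treats as of concern, and at 1% risk even RR = 3 and RR = 4 reach only 17% and 39%.

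A reader might infer more than this, and the documents do not support it:

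- That most harms would be missed overall, or that a non-signal excludes nothing. This would need the joint distribution of cohort sizes and outcome risks, and the article gives no outcome risks. A tested outcome also has a confidence interval, which does exclude some effects.
- That the protocol treats a non-signal as proof of safety. It nowhere says so; its aim is to identify credible signals. Outcomes with fewer than six events in a group are untested, not negative.
- That the RD floor is a power defect. The criteria section presents the thresholds as a deliberate restriction to increases large enough to matter clinically. It needs only to be named where it governs.
- That the lack of a power table is itself a fault. An article may leave that to a fuller document. The fault is that the sentence as written does not match the rule.

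**Conclusion.** The point holds in this limited form. At the 1000-patient floor the written rule would miss a true doubling of risk more often than find it for referent risks of 1% to 5%: detection is about 3% to 35% at 200/800, and at most about 42% over the splits checked. Good detection there requires larger RRs with risks of several percent, or very common outcomes. Low power is therefore not confined to small increases, as the sentence implies.

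The size rests on the assumed RRs, referent risks and splits. It is optimistic in leaving out Benjamini-Hochberg and the cost of weighting. Larger cohorts do better, and no statement about the share of all pair-outcome combinations can be made. No estimate or signal is affected; what changes is how a non-signal may be read. The correction is worth making, but it is one of wording and reporting.

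**What to change.** 1. Reword the sentence in Challenges and Limitations to say that in cohorts near the floor, and for uncommon outcomes, a doubling of risk or more may also be missed.
2. Support it with a short table of the detectable RR under the full rule, by exposed count (for example 200, 583 and 2130) and referent risk. Note that below about 0.3% referent risk the chosen RD floor, not RR 1.33, is the binding criterion.
3. Where results and the visualization tool show non-signals, separate ineligible outcomes (fewer than six events in a group, not tested) from tested non-signals. For the latter show the upper 95% confidence limit of the RR, which the planned models already yield.

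Do not label a non-signal by its 80%-power RR. At 200/800 and 2% risk that RR is 3.6, with SE = ln(3.59/1.33)/2.80 ≈ 0.355. A result that just misses the rule, with a lower limit near 1.33, has an upper limit near 1.33 × exp(3.92 × 0.355) ≈ 5.3, so effects above 3.6 are not excluded.

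The cost is wording, one table and one display field. No new data are needed and the signal rule stays as it is. The stated capability becomes less favourable.

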### Implications for Clinical Practice and Policy

This study has the potential to significantly improve drug safety, particularly in older adults, by identifying harmful DDIs more efficiently. If replicated in other jurisdictions, the findings could provide clinicians with new insights into the risks associated with specific drug combinations, leading to more informed prescribing practices and enhanced patient monitoring. The evidence generated could also inform regulatory agencies, such as Health Canada and the US FDA, helping refine product label warnings and support regulatory decisions. Ultimately, the findings could contribute to safer medication use on a population level, improving medication safety practices worldwide. Moving forward, we will prioritize and verify high-throughput signals across Ontario and beyond, ensuring the continued refinement and application of this approach to achieve more precise and informed medication safety practices.

### Conclusion

This protocol outlines an innovative approach to detecting harmful DDIs in older adults using high-throughput computing and automation. By leveraging Ontario health care data and using advanced analytical techniques, we aim to enhance the efficiency and comprehensiveness of postmarket drug surveillance. The results of this study, if replicated in other jurisdictions, have the potential to significantly improve medication safety, inform clinical practice, and guide regulatory policies. Ultimately, this research aims to reduce the burden of adverse drug events in older adults and lay the foundation for more precise, data-driven medication safety practices worldwide.

## Appendix

Multimedia Appendix 1 Checklist of recommendations for reporting of observational studies using the RECORD (Reporting of Studies Conducted Using Observational Routinely Collected Health Data) statement.

Multimedia Appendix 2 Study variables and the codes used to ascertain baseline comorbidities (sorted alphabetically).

Multimedia Appendix 3 Process of integrating data from different sources.

Multimedia Appendix 4 Overview of the plan to perform the primary analysis and additional exploratory analysis.

Multimedia Appendix 5 Codes for nonoral drugs.

## Abbreviations

ATT: average treatment-effect-in-the-treated
DDI: drug-drug interaction
FDA: Food and Drug Administration
ICES: Institute for Clinical Evaluative Sciences
IPTW: inverse probability of treatment weighting
NNH: number needed to harm
ODB: Ontario Drug Benefit
PAF: population attributable fraction
PD: pharmacodynamic
PHIPA: Personal Health Information Protection Act
PK: pharmacokinetic
RCT: randomized controlled trial
RD: risk difference
REB: Research Ethics Board
RR: risk ratio
SD: standardized difference
SSRI: serotonin reuptake inhibitor
